### Study design

2.1

This is a prospective randomized controlled trial to study the effectiveness and safety of ECMO combined with CRRT in the treatment of fulminant myocarditis. We followed the Consolidated Standards of Reporting Trials (CONSORT) guidelines for reporting randomized trials and provided a CONSORT flow diagram (Fig. 1) and the Standard Protocol Items: Recommendations for Interventional Trials (SPIRIT) 2013 statement.

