### Sample size

2.3

In order to draw reliable conclusions, this study will include as many qualified samples as possible, referring to similar studies,^[8]^ we set the minimum number of people in each group of studies to 40, and the final number will be based on actual recruitment.

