### Observation indicators

2.7

1.Record the patient's basic vital signs changes (such as blood pressure, body temperature, heart rate, etc.), weaning time, hospital stay, etc.;2.Monitor changes in laboratory indicators before and after treatment: such as N terminal pro B type natriuretic peptied, high-sensitivity troponin I, myocardial enzymes, oxygenation index (partial pressure of O_2_/fraction of inspiration O_2_), blood lactic acid (lac), liver and kidney function, coagulation function, arterial blood pH, etc.;3.Echocardiographic indicators: left ventricular ejection fraction (LVEF), left ventricular end-diastolic diameter;4.Complications and treatment outcomes: including weaning rate, in- and out-of-hospital mortality, complication rate (such as infection, bleeding, thrombosis, etc.).5.Sequential Organ Failure Assessment (SOFA)^[14]^ score is used to assess the patient's organ condition.

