### Statistical analysis

2.9

The SPSS 25.0 software was used for statistical analysis. Measurement data are expressed as mean ± standard deviation or median (quartile), and count data are expressed as number of cases. The independent sample *t* test or Mann–Whitney *U* test was used for the comparison of measurement data, the paired *t* test was used for the comparison within the group, and the Chi-Squared test or Fisher exact probability method was used for the comparison of count data. All are two-sided tests, with *P* < .05 as the difference is statistically significant.

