## Discussion

3

Patients with fulminant myocarditis progress rapidly and are often accompanied by difficult to correct hemodynamic disturbances or stubborn fatal arrhythmias. Therefore, the early use of effective mechanical assist devices is the key to improving the prognosis of such patients.^[3,15]^ It has been reported in the literature that the survival rate of mechanical assist devices for fulminant myocarditis is 57% to 80%.^[3,16]^ Early and timely ECMO placement to maintain effective circulatory perfusion is the key to reducing the mortality of FM. However, for long-term use of ECMO treatment, it should be noted that the probability of complications of ECMO treatment such as limb ischemia, abnormal coagulation function, bleeding, and infection will be greatly increased.^[17]^ Some researchers believe that ECMO combined with CRRT avoids the risk of bleeding at the puncture site during ECMO-assisted systemic anticoagulation. At the same time, it can measure the pressure of the ECMO membrane before and after the membrane, reduce the pressure measurement device, and reduce the risk of infection.^[18]^ Studies have shown that during EMCO treatment, about 50% of patients may be combined with CRRT treatment,^[19]^ which may be related to ECMO oxygenated blood flowing backward through the renal artery, ECMO-related inflammation activation, high anticoagulation state, hemolysis, etc. These factors are related.^[20]^ The integrated use of ECMO and CRRT in parallel can achieve joint support of multiple organs such as heart, kidney, and lung in 1 cardiopulmonary bypass pathway. However, some scholars believe that the use of CRRT during ECMO may increase the risk of in-hospital mortality.^[21]^ Therefore, whether the early application of CRRT is beneficial to the prognosis of patients with fulminant myocarditis still needs clinical research to verify.

This study also has the following limitations: the sample size included in this study is limited, which may affect the results. The planned follow-up time for this study is short, and there is no assessment of the long-term efficacy and safety of the treatment plan. If necessary, we will extend the follow-up time and pay more attention to its long-term efficacy.

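### Safety is a stated aim, but deaths and complications are compared only by a P value; at 40 per arm a non-significant result cannot by itself support a safety conclusion, so add risk differences with confidence intervals

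*Protocol article*

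**What the plan says.** Section 2.1 of the protocol article gives the aim as "to study the effectiveness and safety of ECMO combined with CRRT in the treatment of fulminant myocarditis". Section 2.7 lists the outcomes that bear on safety, among them "in- and out-of-hospital mortality, complication rate (such as infection, bleeding, thrombosis, etc". The Discussion names a specific harm in dispute: "some scholars believe that the use of CRRT during ECMO may increase the risk of in-hospital mortality".

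Section 2.9 says how these outcomes are analysed. Count data are summarised as numbers of cases, and "the Chi-Squared test or Fisher exact probability method was used for the comparison of count data". One criterion covers every comparison: "All are two-sided tests, with *P* < .05 as the difference is statistically significant". The article states no risk difference, confidence interval or acceptable excess for any outcome.

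Section 2.3 sets the size: "we set the minimum number of people in each group of studies to 40, and the final number will be based on actual recruitment". The stated basis is "referring to similar studies"; no event rate, effect size or power is given. The limitations paragraph in the Discussion concedes that the sample is limited and that this may affect the results.

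**The concern.** A significance test asks whether the data are incompatible with no difference. A safety aim also asks how large an excess of deaths or complications the data still allow. In a small trial the two questions can have very different answers: P can exceed .05 when there is no harm, and also when there is a moderate or large harm.

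This matters here because the harm is not hypothetical to the authors. They cite a view that CRRT during ECMO raises in-hospital mortality. In the Introduction they also cite a non-significant mortality difference as part of the controversy that motivates the trial. Another non-significant P value without an interval would do little to resolve it, because readers could not see which excess risks had been ruled out.

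**Working it through.** **Inputs**
- Test and level: chi-squared or Fisher, two-sided 0.05 (section 2.9).
- Size: n = 40 per arm, the stated minimum (section 2.3), allocated 1:1 (section 2.5).
- Control mortality: 1 − 0.80 = 20% to 1 − 0.57 = 43%. This is an assumption, taken from the survival range that the Discussion cites for mechanical assist devices.
- Sizes of harm (10 points, 20 points, doubling) and the complication rates below are illustrative assumptions. The article gives none.

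The figure of 40 cannot be reproduced, because the article gives no calculation for it.

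**Step 1: chance of missing a true harm.** Let X and Y be deaths in the control and CRRT arms, independent binomials with n = 40 and probabilities p₁ and p₂. Then

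miss rate = Σ P(X = i) · P(Y = j), over all tables (i, j) that are not significant.

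Chi-squared is taken without continuity correction.

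| True death rates (control → CRRT) | Missed, chi-squared | Missed, Fisher |
|---|---|---|
| 10-point rise: 20% → 30% | 82% | 88% |
| 30% → 40% | 85% | 90% |
| 43% → 53% | 84% | 89% |
| 20-point rise: 20% → 40% | 50% | 59% |
| 30% → 50% | 54% | 63% |
| 43% → 63% | 54% | 63% |
| Doubling: 20% → 40% | 50% | 59% |
| 30% → 60% | 20% | 28% |
| 43% → 86% | 1% | 2% |

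The absolute rises are missed at similar rates across the whole mortality range. The doubling is not: how often it is missed depends strongly on the base rate.

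For a complication whose rate doubles, the miss rate (chi-squared / Fisher) is 75% / 84% from 10% to 20%, and 63% / 72% from 15% to 30%.

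**Step 2: one table.** Take 8/40 deaths in the control arm and 16/40 in the CRRT arm. The pooled proportion is 24/80 = 0.30, so

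χ² = (0.40 − 0.20)² / (0.30 × 0.70 × 2/40) = 0.04 / 0.0105 = 3.81,

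which gives P = 0.051; Fisher gives P = 0.087. Neither is significant.

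**Step 3: what an interval adds.** Let d be the CRRT proportion p_T minus the control proportion p_C, and (l, u) the Wilson 95% limits for each arm. The Newcombe limits are

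lower = d − √[(p_T − l_T)² + (u_C − p_C)²]

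upper = d + √[(u_T − p_T)² + (p_C − l_C)²].

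For 8/40 in each arm the Wilson limits are 0.105 and 0.348, so upper = √(0.148² + 0.095²) = 0.176.

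| Deaths, CRRT v control (of 40 each) | 95% Newcombe interval for the excess |
|---|---|
| 16 v 8 | −0.1 to +38.1 points |
| 8 v 8 | ±17.6 points |
| 12 v 12 | ±19.5 points |
| 17 v 17 | ±20.7 points |
| 10 v 12 | upper limit +14.3 points |
| 8 v 12 | upper limit +9.0 points |

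All six tables are non-significant, yet the upper limit of the excess runs from 9 to 38 points. The P value rule treats them alike; the interval separates them.

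**The case against.** The strongest counter-argument is that nothing in the article equates P above .05 with safety. Section 2.9 says only when a difference counts as significant. That stands. A reader might infer that a non-significant result would be reported as showing the combination to be safe, but the text does not say so, and this point does not rest on it.

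A reader might also infer that even a doubling of deaths would usually go undetected. Step 1 shows this to be so only near the bottom of the mortality range. From 30% a doubling is detected 72% to 80% of the time, and from 43% it is detected 98% to 99% of the time.

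Other parts of the objection also hold:
- Forty is a floor. The authors intend to recruit as many as they can, so the final power may be higher. Still, nothing commits them to more than 40.
- The tests are two-sided, so a significant reduction in deaths or complications with CRRT is also possible. A non-significant P value is not the only reassuring result available.
- The limitations paragraph already admits a limited sample, though without saying what that means for safety.
- A full protocol or analysis plan that is not shown may contain intervals. The point is therefore confined to the summary format and criterion that the article itself states.

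Finally, it would be wrong to declare in advance that 40 per arm cannot exclude an excess of about 20 points. That depends on the data: 8/40 (CRRT) against 12/40 (control) gives an upper limit of +9 points.

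**Conclusion.** The point holds as an improvement to the stated analysis, not as an error that invalidates the trial. The article pairs a safety aim with a P-value-only comparison. At its minimum size, that comparison misses a true 20-point rise in deaths at least half the time and a 10-point rise more than four times in five, throughout the assumed control mortality of 20% to 43%. A non-significant result therefore cannot by itself support a safety conclusion.

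The figures rest on exactly 40 evaluable patients per arm, on the cited survival range applying to the control arm, and on illustrative sizes of harm. More patients would lower the miss rates.

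**What to change.** **Section 2.9.** Keep the tests. For mortality and for infection, bleeding and thrombosis, add events/N per arm and the risk difference (CRRT arm minus control) with its two-sided 95% Newcombe interval. State that safety will be described by the upper confidence limit of the excess risk, and that a non-significant P value will not be taken as evidence of safety.

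**Discussion, existing limitations paragraph.** Add that if observed mortality were equal in the two arms at 40 per arm, the 95% interval would still allow an excess of about 18 to 21 points. Do not name a fixed excess that the trial cannot exclude.

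**Cost.** One extra interval per outcome and a few sentences, with no additional patients, visits or data. The downside is a more modest safety claim.

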### Study design

2.5

Eligible participants were randomly assigned to the treatment group or the control group at a ratio of 1:1 using a random tool based on the central network. Randomization was performed without any stratification generated by an independent statistician who was not involved in trial implementation or statistical analysis using SAS 9.3 software (SAS Institute, Cary, NC). The clinical research coordinator entered the participant information on the tablet, and was given a random number. The research assistant gets the participant's assignment from the computer. Throughout the research process, the research assistant is responsible for screening, recruiting participants, and assigning random numbers to the included participants. The result assessor is responsible for the assessment of the scale.

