### Data collection and management

2.8

Observation indicators were collected before treatment, 24 hours, 48 hours, 72 hours, 96 hours after treatment, and 2 hours before weaning. At the same time, follow-up for 30 days to assess complications and treatment outcome. One or 2 assistants will collect and record the entire data. Personal information about potential participants and registered participants will be collected, shared and stored in an independent storage room to protect confidentiality before, during and after the test. The access to the database will be restricted to the researchers in this study team.

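### No outcome or time point is primary, and at least 23 equally ranked indicators are all judged at two-sided P < .05, so the chance of a spurious significant result is far above 5%

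*Protocol article*

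**What the plan says.** - **Outcomes (section 2.7).** There are five groups of indicators, none ranked above another. They include "basic vital signs changes (such as blood pressure, body temperature, heart rate, etc.), weaning time, hospital stay, etc"; a set of laboratory values introduced by "Monitor changes in laboratory indicators before and after treatment"; two echocardiographic measures; a fourth group, "Complications and treatment outcomes: including weaning rate, in- and out-of-hospital mortality, complication rate (such as infection, bleeding, thrombosis, etc"; and the SOFA score. Three of the five lists are open-ended.
- **Timing (section 2.8).** "Observation indicators were collected before treatment, 24 hours, 48 hours, 72 hours, 96 hours after treatment, and 2 hours before weaning". Complications and treatment outcome are followed for 30 days. The starting point of the 30 days is not given.
- **Decision level (section 2.9).** "All are two-sided tests, with *P* < .05 as the difference is statistically significant". Between-arm tests and within-arm paired t tests come under the same sentence.
- **Size (section 2.3).** "we set the minimum number of people in each group of studies to 40, and the final number will be based on actual recruitment". Allocation is 1:1 (section 2.5).

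Neither the abstract nor sections 2.3, 2.7 and 2.9 name a primary outcome or a primary time point.

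**The concern.** A 5% significance level protects one test chosen in advance. Here many tests share that level and none is set apart, so the plan never says which result would settle whether adding CRRT to ECMO helps. A transient laboratory difference would have the same standing as a difference in deaths, and the choice of which to put forward could be made after the data are seen.

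This matters more here for two reasons. The Discussion reports a view that CRRT during ECMO may raise in-hospital mortality, so markers and mortality could plausibly point in opposite directions. And some laboratory values are close to what CRRT acts on directly: the Introduction describes it as replacing renal function and removing toxins, and section 2.6 has nurses adjust pump speed to the acid-base result. A difference in kidney function or pH may therefore be a real, direct effect of the machine without being a benefit to the patient.

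**Working it through.** **The plan's own figure.** The minimum of 40 per group cannot be reproduced. Section 2.3 takes it from similar studies and gives no outcome, event rate, effect size, standard deviation or power.

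**Counting the comparisons (named items only, section 2.7).**
- Serial indicators: 3 vital signs + 9 laboratory items or panels + 2 echocardiographic + SOFA = 15.
- Single outcomes: weaning time, hospital stay, weaning rate, in-hospital death, out-of-hospital death, infection, bleeding, thrombosis = 8.
- Each indicator tested once: 15 + 8 = 23.
- Serial indicators tested at each of the five post-baseline times in section 2.8: 15 × 5 + 8 = 83.

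Panels such as myocardial enzymes count once, and the within-arm paired tests are left out.

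**Chance of at least one false positive if nothing differs, independent tests: 1 − 0.95^k.**
- k = 8 (single outcomes only): 1 − 0.95^8 = 33.7%.
- k = 23: 1 − 0.95^23 = 69.3%; expected number 23 × 0.05 = 1.15.
- k = 83: 1 − 0.95^83 = 98.6%; expected number 83 × 0.05 = 4.15.

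**Allowing for correlation.** Test statistics were simulated (100,000 runs) with an assumed correlation between indicators and, for the 83-test case, a higher one between times of the same indicator.

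| Between indicators | Between times | 23 tests | 83 tests |
|---|---|---|---|
| 0.1 | 0.5 | 67.7% | 95.9% |
| 0.2 | 0.6 | 63.9% | 92.6% |
| 0.3 | 0.7 | 58.3% | 86.1% |
| 0.5 | 0.8 | 44.9% | 67.5% |
| 0.7 | 0.9 | 30.7% | 42.8% |

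Taking 0.2 to 0.3 as moderate, the range runs from 58% (23 tests, 0.3) to 93% (83 tests, 0.2). At 0.7 it is 31% to 43%.

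**After the fix.** One outcome named in advance and tested once has a 5% error. If every comparison stayed confirmatory, a Bonferroni level would be 0.05/23 = 0.0022 or 0.05/83 = 0.0006.

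**Power if death were primary, n = 40 per arm.** The Discussion cites survival of 57% to 80% with mechanical assist devices, that is, mortality of 43% to 20%. This is background, not a design input. With m the mean of p1 and p2, power = Φ{(|p1 − p2| − 1.96 √[2m(1 − m)/n]) / √[(p1(1 − p1) + p2(1 − p2))/n]}.
- 43% v 20%: (0.23 − 1.96 × 0.1039)/0.1006 = 0.26, power 60%.
- 43% v 33%: (0.10 − 1.96 × 0.1085)/0.1080 = −1.04, power 15%.
- 20% v 10%: (0.10 − 1.96 × 0.0798)/0.0791 = −0.71, power 24%.

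For 80% power, the same contrasts need 63, 369 and 199 per arm.

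**The case against.** **An unseen SAP may deal with it.** It may hold a multiplicity adjustment, and the absence of one is not the point here. The primary outcome is different: it defines the question and the sample size rests on it. This article has sections on outcomes, sample size and analysis, and what they set down is an unranked list with one threshold.

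**The no-effect assumption is doubtful for some indicators.** This stands. If CRRT shifts kidney function or pH directly, a significant difference there is not a false positive, so the expected counts of 1.15 and 4.15 are too high to that extent. It supports the same remedy, because such differences should not carry the efficacy conclusion.

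**Stronger readings that the document does not support:**
- *A false positive is close to certain.* That needs all 83 comparisons and weak correlation. Section 2.8 says when data are collected; section 2.9 does not say that each time is tested.
- *Any P < .05 will be declared proof of efficacy.* Section 2.9 defines only when a difference is statistically significant. The defect is that no rule links the tests to a conclusion.
- *The open sample size inflates the error.* Section 2.3 says "the final number will be based on actual recruitment", which ties the number to recruitment, not to results, and no interim looks are stated. If closure is blind to results, the error stays at 5%. Purely as illustration, unadjusted looks at 40 and 60 per arm would give 7.8%, and looks at 40, 50, 60, 70 and 80 would give 11.1%. The restriction of database access to the study team is a confidentiality statement, not evidence of looks.
- *Mortality is split so that the out-of-hospital part depends on leaving hospital alive.* The wording can equally mean all deaths wherever they occur. Counting one death outcome lowers the totals only to 22 and 82: 1 − 0.95^22 = 67.6% and 1 − 0.95^82 = 98.5%.

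**Conclusion.** The point holds. The protocol fixes no confirmatory test, and any one of many results could stand as the trial's finding. With no effect on any outcome, every scenario examined over the full set of indicators puts the chance of at least one significant between-arm result at about six times the nominal 5% or more (31% at the lowest). Where it lies between 31% and 99% depends on the correlations and on how many times are tested, neither of which the article states. The open sample size is a secondary matter: it leaves room for inflation but does not cause it.

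**What to change.** - **Sections 2.7 and 2.9.** Name one primary outcome and one time point. An example is all-cause death by 30 days from randomisation, wherever it occurs. Follow-up for 30 days is already planned, but its origin has to be stated. Which outcome to choose is the sponsor's decision. Test only that outcome at two-sided .05. Report every other indicator as secondary or exploratory, with estimates and 95% confidence intervals and no efficacy claim.
- **Section 2.3.** State that recruitment closes by a rule blind to outcome data, either a date or a number. The sponsor need not settle on the present minimum.

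**Cost.** The change is to wording and needs no further data collection. Secondary markers can then no longer be offered as proof of efficacy. If death is chosen, the protocol should disclose the low power at 40 per arm: about 60% for 43% versus 20%, and 15% to 24% for the 10-point differences shown. That limitation exists already; naming the outcome makes it visible.

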## Discussion

3

Patients with fulminant myocarditis progress rapidly and are often accompanied by difficult to correct hemodynamic disturbances or stubborn fatal arrhythmias. Therefore, the early use of effective mechanical assist devices is the key to improving the prognosis of such patients.^[3,15]^ It has been reported in the literature that the survival rate of mechanical assist devices for fulminant myocarditis is 57% to 80%.^[3,16]^ Early and timely ECMO placement to maintain effective circulatory perfusion is the key to reducing the mortality of FM. However, for long-term use of ECMO treatment, it should be noted that the probability of complications of ECMO treatment such as limb ischemia, abnormal coagulation function, bleeding, and infection will be greatly increased.^[17]^ Some researchers believe that ECMO combined with CRRT avoids the risk of bleeding at the puncture site during ECMO-assisted systemic anticoagulation. At the same time, it can measure the pressure of the ECMO membrane before and after the membrane, reduce the pressure measurement device, and reduce the risk of infection.^[18]^ Studies have shown that during EMCO treatment, about 50% of patients may be combined with CRRT treatment,^[19]^ which may be related to ECMO oxygenated blood flowing backward through the renal artery, ECMO-related inflammation activation, high anticoagulation state, hemolysis, etc. These factors are related.^[20]^ The integrated use of ECMO and CRRT in parallel can achieve joint support of multiple organs such as heart, kidney, and lung in 1 cardiopulmonary bypass pathway. However, some scholars believe that the use of CRRT during ECMO may increase the risk of in-hospital mortality.^[21]^ Therefore, whether the early application of CRRT is beneficial to the prognosis of patients with fulminant myocarditis still needs clinical research to verify.

This study also has the following limitations: the sample size included in this study is limited, which may affect the results. The planned follow-up time for this study is short, and there is no assessment of the long-term efficacy and safety of the treatment plan. If necessary, we will extend the follow-up time and pay more attention to its long-term efficacy.
